# **Protocol for a multicenter, real-world study of HIV pre-exposure prophylaxis among men who have sex with men in China (*CROPrEP*)**

## **Research objectives**

The objectives of the *CROPrEP* project are to assess among HIV-negative Chinese MSM:

1. The real-life effectiveness of daily or event-driven PrEP use
2. Adherence to PrEP
3. Safety and tolerability
4. The potential effects of PrEP use on sexual behaviors and incidence of sexually transmitted infections (STIs)

## **Methods/Design**

### **Overview of study design**

As shown in Fig 1, the *CROPrEP* project is a multicenter, real-world, prospective cohort study with two arms of daily or event-driven TDF/FTC as PrEP among HIV-negative MSM at high risk of HIV infection in China. This study is being conducted in four metropolitan Chinese cities, which have moderate to high prevalence of HIV among MSM: Shenyang, Beijing, Shenzhen, and Chongqing. In total, 1023 eligible participants will be permitted to choose between daily or event-driven PrEP, based on their preference. Participants will be prospectively followed for 12 months, with quarterly clinic visits, and online weekly notes. The PrEP intervention, in combination with a package of prevention services, will be provided to participants (e.g., free adherence supporting reminders and counseling, sexual health education, panel management by peer counselors, and referrals to relevant clinics for individuals who test positive for either HIV or syphilis). These four study centers have also established

an expanding cohort study of 500 HIV-1-negative MSM for epidemic surveillance and estimation, which can be considered a natural background control for PrEP users, to evaluate the efficacy of PrEP use.

[figure not shown]

Fig. 1 Flow chart of study design

PrEP users will be permitted to switch their PrEP regimen. PrEP nonusers can initiate PrEP at any time if they want.

### Sample size

Given the well-documented protective effect of PrEP, the *CROPrEP* project is considered a demonstration project, and the sample size is not determined by power calculations. Based on preliminary survey data of acceptance among MSM in China, the sample size was increased as far as possible, on the basis of fully considering the population of each research center, and a largest sample size of 1000 chosen.

### Project promotion and recruitment of participants

Participant recruitment is performed by both online and offline methods. Online methods rolled out through accounts managed by each research center include advertising on public social platforms, such as Weibo and WeChat. Offline recruitment methods include the following: (1) clinic-based sampling:

each study center collaborates with the local CDC and clinic staff will recruit MSM who already attend voluntary counseling and testing clinics, are at high risk of HIV infection, and are willing to participate in the *CROPrEP* after learning about the study; (2) community-based sampling: each study center collaborates with local MSM community-based organizations (CBOs) to recruit MSM in the community; (3) venue-based sampling: eligible MSM will be recruited from suitable venues (e.g., MSM parks, bars, clubs, and bathhouses) through outreach activities; and (4) peer referrals: potential participants will be encouraged to recruit their friends who are MSM or their male partners to participate in this study. All candidates will be preregistered and then invited for a screening visit at the local study center on the principle of competitive enrollment. Prior to the eligibility assessment for the study, written informed consent will be obtained from all participants. PrEP nonusers will be recruited using the same way as PrEP users.

### **Participant eligibility and enrollment**

As shown in Table 1, the inclusion and exclusion criteria will be used to assess the eligibility of participants in the *CROPrEP* project. These criteria are established by an expert group of researchers, clinicians, and CBO representatives, based on international guidelines on PrEP and the behavior characteristics of MSM in China.

Eligibility will be assessed for ongoing comprehensive screening at a clinic, including laboratory testing for antibodies and RNA for HIV, syphilis, hepatitis B virus surface antigen (HBsAg), bone mineral density (BMD), renal and liver function, clinical evaluation with family or personal medical history, concomitant treatment by an experienced physician, and a self-administered questionnaire, to assess sociodemographic factors, current sexual behavior, substance use, and social and psychological information, on their mobile phones. Confirmed eligible participants will be invited to return to the

clinic within a week to choose a regimen and receive a supply of TDF/FTC and detailed instructions for PrEP use.

**Table 1 Inclusion and exclusion criteria for participants in the CROPrEP project**

**Inclusion criteria**

- Aged 18–65 years old\*
- Born to male sex\*
- Test results demonstrate HIV negative\*
- Had sex with a man in the last 6 months\*
- **Behavioral eligibility criteria**\*

Participants of male sex at birth and who have sex with men, reporting at least one criterion associated with high risk for HIV infection in the 6 months prior to enrolment as follows:

- Unprotected (condom-less) receptive anal intercourse with male partners
- More than two male partners (regardless of condom use and HIV serostatus)
- Reported STI, such as syphilis, HSV-2, gonorrhea, chlamydia, chancroid, or lymphogranuloma venereum
- Reported a history of post-exposure prophylaxis

Note: Individuals in a monogamous relationship with an HIV-1 seronegative partner or a virologically suppressed HIV-1+ partner for > 1 year will not be eligible for participation.

- Through comprehensive physical examination, including routine urine examinations, hepatic and renal function tests, blood glucose and lipids, and BMD; no serious liver or kidney dysfunction and negative for HBs antigen, without serology indicating osteoporosis, and other indicators are normal
- Able and being willing to sign written informed consent and participate in the study as procedures require\*
- Chinese citizens\*

**Exclusion criteria**

- HIV-1 infected, or having clinical signs or symptoms consistent with acute viral infection\*
- Atopic individual or allergic to the ingredients of the experimental drug or ART\*
- Having serious chronic disease, including metabolic diseases (such as diabetes), neurological, and psychiatric disorders
- Weight < 40 kg or > 140 kg\*
- Having osteoporosis: aged  $\geq 50$  years with BMD T-score  $\leq -2.5$ ; aged < 50 years with BMD

Z-score  $\leq -2$  and fragility fracture

- Mental health issues which may compromise participant adherence or safety, including memory loss, cognitive impairment, intellectual disability, or communication disorders
- Currently, or 30 days prior to enrolment, taking interferon, interleukin, or other immunoregulators\*

- Currently taking products containing antiretrovirals\*
  - Participating in another research study related to HIV and antiretroviral therapy or other intervention study\*
- 

PrEP participants need to meet all eligibility criteria;

\*Eligibility criteria for PrEP nonusers.

### **Drug regimen and provision**

The PrEP used in the *CROPrEP* project is Truvada®; one film-coated pill contains 200 mg of FTC and 300 mg of TDF. Participants will receive free Truvada and can choose between taking PrEP on a daily basis, or according to an event-driven regimen, before and after anal sex. The daily dosing regimen is one Truvada pill every 24 h. The event-driven regimen is two Truvada pills 2–24 h before sexual intercourse (or one pill if the last medication was taken 1 to 6 days ago), a pill every 24 h from the first drug intake during the period of sexual activity, including after the last sexual intercourse, and one final Truvada pill approximately 24 h later. PrEP users will be permitted to switch their PrEP regimen during the study period. All PrEP users followed such advice. PrEP nonusers will be followed up at the same clinic. They can initiate PrEP at any time if they want.

### **Study visits**

Each PrEP participant will be followed up for 12 months and will experience a total of six clinic visits at centers (including screening (baseline) and follow-up (FU) at 1, 3, 6, 9, and 12 months) (Table 2). PrEP nonusers should complete four quarterly follow-up visits for a year. The visit window for this study is 7 days. For each clinic visit, adverse events and concomitant medication will be documented and HIV/STI testing and monitoring of biological indices for PrEP-related toxicity performed by experienced physicians. Participants will be instructed to complete an online self-administered questionnaire to assess behaviors, psychological status, adherence, side effects, and attitude towards PrEP use in a separate private interview room. Dry blood spots and blood samples will be collected

from participants who report that they have taken PrEP during the follow-up interval for TDF/FTC concentration and HIV/STI testing, alongside other clinical evaluations. Participants will be required to return the leftover TDF/FTC to the clinic in exchange for a refill to cover their needs until the next clinic visit.

Online weekly notes will be sent to the mobile phones of participants weekly, to feedback their short-term pill use and sexual practices. Participants will be instructed to complete the message every week, to limit recall bias.

During the follow-up period, researchers will benefit from leveraging CBOs and the internet to strengthen group- and individual-level supervision of adherence to medication and cohort management. This multifaceted strategy will include a panel of CBO counselors, providing interactive peer counseling focusing on study retention; a Short Message Service application, providing routine online medication reminders and follow-up visit reminders, along with a live chat; and clinicians and study staff, providing one-on-one personalized compliance support, counseling, and cohort maintenance.

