**Table 2 Schedule of the *CROPrEP* project**

| Procedures                   | Screening/
Enrollment | FU
1 m±7d# | FU
3 m±7d | FU
6 m±7d | FU
9 m±7d | FU
12 m±7d |
|-------------------------------------|----------------------------------|----------------------------------|----------------------|----------------------|----------------------|-----------------------|
| Informed consent *       | ×                                |                                  |                      |                      |                      |                       |
| Self-administrated questionnaire    | ×                                | ×                                | ×                    | ×                    | ×                    | ×                     |
| Interviews                   |                                  |                                  |                      |                      |                      |                       |
| Relevant medical history            | ×                                |                                  |                      |                      |                      |                       |
| Current/concomitant medication      | ×                                | ×                                | ×                    | ×                    | ×                    | ×                     |
| Adverse events or side effects      |                                  | ×                                | ×                    | ×                    | ×                    | ×                     |
| Medication return and allocation    | ×                                | ×                                | ×                    | ×                    | ×                    | ×                     |
| HIV/STIs testing* |                                  |                                  |                      |                      |                      |                       |
| HIV screening                       | ×                                | ×                                | ×                    | ×                    | ×                    | ×                     |
| HIV Western Blot a       | ×                                | ×                                | ×                    | ×                    | ×                    | ×                     |

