#### *Adherence lab assessment*

|                          |  |   |   |   |   |   |
|--------------------------|--|---|---|---|---|---|
| Blood drug level testing |  | × | × | × | × | × |
|--------------------------|--|---|---|---|---|---|

Abbreviations: FU, follow-up; m, month(s); d, day. a Items that PrEP nonusers need to complete. # PrEP nonusers do not need to attend this follow-up visit. a Anyone who screens positive for HIV will have the results confirmed by western blotting. b Anyone who screens negative for HIV will have the results confirmed by HIV RNA pooling PCR test. c Anyone who tests positive for HIV will have their samples further tested for HIV resistance and viral load.

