### **Laboratory Procedures**

As summarized in Table 3, during each clinical visit, participants will be asked to provide blood and urine specimens for monitoring of HIV infection, STIs, and objective measures for adherence and safety of PrEP use. Analysis of blood TDF/FTC concentrations will be performed in the Key Laboratory of AIDS Immunology of National Health Commission, Department of Laboratory Medicine, The First Affiliated Hospital, China Medical University, in Shenyang, China. All other testing will be conducted by nationally certified laboratories, located at each research center. Dry blood spots and serum samples will be collected at every visit for TDF/FTC drug level testing.

If a participant is found to have seroconverted to HIV, his participation in the study will be terminated immediately and he will be called for a final visit. At the final visit, study staff will collect unused pills, conduct resistance and viral load testing, and provide referrals to an HIV clinic for treatment. The study staff will report each case of seroconversion to the sponsor.

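### The Study visits section makes blood sampling for drug level and HIV/STI testing depend on reported PrEP use, against Table 2 and Laboratory Procedures; the drug-level measure is the one exposed

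*Protocol*

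**What the plan says.** The protocol states the sampling rule in several places, and they do not agree.

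- **Study visits, conditional sentence.** Dried blood spots and blood samples are collected "from participants who report that they have taken PrEP during the follow-up interval for TDF/FTC concentration and HIV/STI testing". The condition is reported use, not membership of the PrEP group, and as worded it covers both drug level and HIV/STI testing.
- **Study visits, preceding text.** HIV/STI testing is to be done at each clinic visit, along with safety recording and toxicity monitoring. This has no condition.
- **Laboratory Procedures.** The section opens by stating that "during each clinical visit, participants will be asked to provide blood and urine specimens for monitoring of HIV infection, STIs, and objective measures for adherence". Further on, the same paragraph says: "Dry blood spots and serum samples will be collected at every visit for TDF/FTC drug level testing". Neither is conditional.
- **Table 2.** The row "Blood drug level testing" is marked at months 1, 3, 6, 9 and 12. The row "HIV screening" is marked at screening and at all five follow-up visits, as are RNA pooling PCR and syphilis. No row or footnote refers to reported use.
- **Table 2 footnote.** The HIV/STI block heading carries an asterisk, and a footnote reads "Items that PrEP nonusers need to complete". The footnote's mark is unclear in the text as read, but it is probably that asterisk. If so, men who take no PrEP are tested for HIV and syphilis by design.

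Table 4 lists drug concentration in blood as an adherence end point, alongside self-report, weekly messages and pill counts. It sets no threshold, proportion or denominator for the concentration measure.

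**The concern.** Drug concentration is the measure that does not depend on what a man says about his pill-taking, and the protocol intends to compare it with the self-reported sources. If blood is drawn only after a man reports use, the self-report decides whether the objective check takes place. Enrolled users who stopped, or who report no use for an interval, then have no concentration result.

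This is a specimen-collection rule, so it cannot be left to the analysis stage: blood not drawn cannot be assayed later. A site could reasonably treat the specific condition in Study visits as limiting the general statement in Laboratory Procedures, and nothing in the protocol says which governs. Centres could therefore follow different rules.

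The filter may also act unequally between regimens. Event-driven dosing follows sex, so intervals without use are plausibly commoner in that group.

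**Working it through.** There is no plan figure to reproduce: the protocol gives no adherence or incidence rate, and it states that the sample size does not come from a power calculation. The check is a comparison of the provisions, followed by an illustration on assumed inputs.

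**1. Who is sampled under each provision**

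| Provision | Drug level | HIV/STI testing |
|---|---|---|
| Study visits, conditional sentence | only men reporting PrEP use in the interval | only men reporting PrEP use in the interval |
| Study visits, preceding text | not addressed | each clinic visit |
| Laboratory Procedures | every visit | each visit |
| Table 2 | months 1, 3, 6, 9, 12 | screening and months 1, 3, 6, 9, 12 (month 1 not for nonusers) |

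For drug level, one provision stands against two. For HIV/STI testing, it stands against three, one of them in its own section. Applied literally it would also exempt PrEP nonusers from HIV testing, which cannot be meant because they form the comparison group for HIV incidence.

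**2. Drug level, if the conditional sentence is followed**

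Let *a* be the share of sampled visits with detectable (or protective) drug and *q* the share of PrEP-user visits with no reported use. Assume that no-use visits have no drug.

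- Share among those sampled: *a*
- Share over all attended visits: *a*(1 − *q*)
- Overstatement: *a* − *a*(1 − *q*) = *aq*

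With *a* = 0.80 (assumed):

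| *q* (assumed) | Sampled only | All visits | Difference |
|---|---|---|---|
| 0.10 | 80% | 0.80 × 0.90 = 72% | 8 points |
| 0.20 | 80% | 0.80 × 0.80 = 64% | 16 points |
| 0.30 | 80% | 0.80 × 0.70 = 56% | 24 points |

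Over *a* from 0.50 to 0.90 and *q* from 0.05 to 0.30, the difference runs from 0.50 × 0.05 = 2.5 points to 0.90 × 0.30 = 27 points. If some men who report no use do have drug in blood, at rate *b*, it shrinks to *q*(*a* − *b*).

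**3. HIV ascertainment, only if the sentence overrode the other three provisions**

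Assume 1000 man-years, 20% of time off PrEP at 5 per 100 person-years, and the rest at 1 per 100.

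- Infections on PrEP: 1000 × 0.8 × 0.01 = 8. Off PrEP: 1000 × 0.2 × 0.05 = 10. Total: 18.
- If the same men are off PrEP throughout and never tested, 8 of 18 are seen.
- If reported use is redrawn independently each quarter, an off-PrEP infection is missed only if the man reports no use at every remaining visit. Missed: (10/4) × (1 + 0.2 + 0.2² + 0.2³) = 2.5 × 1.248 = 3.12. Seen: 18 − 3.12 = 14.88, a loss of 3.12/18 = 17%.
- If HIV testing follows Table 2, Laboratory Procedures and the preceding text of Study visits, none are lost to this rule.

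**The case against.** The strongest reply is that the outlying sentence is loose drafting, perhaps meant only to spare PrEP nonusers a drug assay, and that Table 2 would govern in practice. That is plausible, and it means the bias is conditional rather than established. It does not rescue the wording, because the sentence turns on reported use and so also removes enrolled users who stopped.

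A reader might infer that seroconversions are undercounted and effectiveness overstated. The documents do not support that as a consequence of the plan, since three provisions require HIV/STI testing at each visit. A reader might also calculate that 1.0 of 1.8 infections per 100 person-years (56%) would be missed on the inputs in step 3. That figure counts infections arising in untested intervals. HIV infection persists and would be found at any later tested visit, so a 56% loss needs the same men never to be tested again.

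Other limits on the adherence point also stand:

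- It concerns the concentration measure alone.
- The condition is any use in the interval, so poor adherers who report some use, and men who over-report, are still sampled.
- Table 4 fixes no proportion or denominator, so the analysis could count reported non-use as no drug. That would remove the arithmetic bias, but by substituting self-report for the measurement meant to check it.
- An event-driven user who had no sex takes no pills and is not non-adherent. The all-visit percentages above therefore describe drug presence, not adherence to the chosen regimen.

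**Conclusion.** The point holds as an internal contradiction that needs correcting. The Study visits sentence conflicts with Laboratory Procedures and Table 2 on who gives blood for drug levels. On HIV/STI testing it conflicts with both of those and with its own section.

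The exposed result is concentration-based adherence, which would tend to be overstated if the sentence were followed. The size is illustrative: 8, 16 or 24 points at *a* = 80% and *q* = 10, 20 or 30%, with no drug assumed at no-use visits. None of these inputs comes from the protocol. HIV ascertainment is a secondary exposure that exists only if the sentence is applied literally; under the other provisions its bias is zero.

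**What to change.** Rewrite the conditional sentence in Study visits to agree with Table 2 and Laboratory Procedures:

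- Define drug-level sampling by enrolment as a PrEP user, at each follow-up visit, whatever use is reported. Say when a nonuser who starts PrEP enters that group.
- Remove HIV/STI testing from the conditional sentence, leaving it to the text that already places it at each clinic visit.
- Align the timing in Laboratory Procedures, which says every visit, with Table 2, which schedules no drug level at screening.
- Summarise drug levels over all attended PrEP-user visits. Show visits with no reported use separately and, for event-driven users, whether sex was reported in the interval, so that absence of drug is not read as non-adherence.

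The cost is one protocol sentence and some LC-MS assays for men reporting no use. Table 2 already schedules those assays, and blood is already drawn at the same visits for HIV testing.

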**Table 2 Schedule of the *CROPrEP* project**

| Procedures                   | Screening/
Enrollment | FU
1 m±7d# | FU
3 m±7d | FU
6 m±7d | FU
9 m±7d | FU
12 m±7d |
|-------------------------------------|----------------------------------|----------------------------------|----------------------|----------------------|----------------------|-----------------------|
| Informed consent *       | ×                                |                                  |                      |                      |                      |                       |
| Self-administrated questionnaire    | ×                                | ×                                | ×                    | ×                    | ×                    | ×                     |
| Interviews                   |                                  |                                  |                      |                      |                      |                       |
| Relevant medical history            | ×                                |                                  |                      |                      |                      |                       |
| Current/concomitant medication      | ×                                | ×                                | ×                    | ×                    | ×                    | ×                     |
| Adverse events or side effects      |                                  | ×                                | ×                    | ×                    | ×                    | ×                     |
| Medication return and allocation    | ×                                | ×                                | ×                    | ×                    | ×                    | ×                     |
| HIV/STIs testing* |                                  |                                  |                      |                      |                      |                       |
| HIV screening                       | ×                                | ×                                | ×                    | ×                    | ×                    | ×                     |
| HIV Western Blot a       | ×                                | ×                                | ×                    | ×                    | ×                    | ×                     |
| HIV RNA Pooling PCR b    | ×                                | ×                                | ×                    | ×                    | ×                    | ×                     |
| HIV resistance testing c |                                  |                                  |                      |                      |                      |                       |
| HIV-1 viral load c       |                                  |                                  |                      |                      |                      |                       |
| Syphilis                            | ×                                | ×                                | ×                    | ×                    | ×                    | ×                     |

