### **Safety assurance**

All PrEP users should receive safety assurance at each follow-up. Safety of TDF/FTC will be monitored by laboratory ratings, based on vital signs and adverse events recorded on a paper case report form at each clinic visit, and the results of causal association and severity assessment will be independently evaluated by two physicians. Any reported adverse events will be clinically tracked until they are restored or stabilized. Serious adverse events are life-threatening events, including HIV

seroconversions that must be reported to the sponsor within one business day, and the lead ethics committee within 72 h.

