### **3. Safety and tolerability:**

- Rate of side effects or adverse events related to PrEP use
- Rate of adverse events related to discontinuation of PrEP or switching PrEP regimens

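### No structured symptom baseline is scheduled before PrEP starts, and the protocol does not say whether self-reported side effects are judged for causality before they enter the single safety rate

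*Protocol*

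**What the plan says.** Safety and tolerability is the third research objective. Its first end point in Table 4 is "Rate of side effects or adverse events related to PrEP use".

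Four parts of the protocol bear on how that rate is built:

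- **Table 2.** The row "Adverse events or side effects", in the interview block, has no tick at Screening/Enrollment and ticks at months 1, 3, 6, 9 and 12. It does not carry the mark for items that nonusers complete. The self-administered questionnaire is a separate row and is ticked at screening.
- **Participant eligibility and enrollment.** The screening questionnaire is used "to assess sociodemographic factors, current sexual behavior, substance use, and social and psychological information, on their mobile phones".
- **Study visits.** The questionnaire described here is an "online self-administered questionnaire to assess behaviors, psychological status, adherence, side effects, and attitude towards PrEP use". The same section says: "For each clinic visit, adverse events and concomitant medication will be documented". It counts "a total of six clinic visits at centers (including screening (baseline) and follow-up (FU) at 1, 3, 6, 9, and 12 months".
- **Safety assurance.** Adverse events go on a paper case report form, and "the results of causal association and severity assessment will be independently evaluated by two physicians".

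Data collection and quality assurance lists side effects among the data from the questionnaire platform and says that the data sources will be triangulated, without saying how.

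**The concern.** Minor complaints of the kind a side-effect question picks up also occur in people who take no drug. Two references could separate them from drug effects: the participant's own record before the first pill, or the same questions put to men not on PrEP. The protocol schedules neither in structured form. What remains is case-by-case judgement of causality, and it is not stated that this judgement reaches the questionnaire reports.

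The result at stake is the tolerability rate, which Study end points presents as part of the evidence on implementing PrEP in China. Separate reporting of the two sources can be arranged later in an analysis plan. A symptom record from before the drug cannot be created once a participant has started.

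**Working it through.** The protocol states no expected side-effect rate, so there is no figure to reproduce. The check is first a comparison of the text, then an illustration with assumed inputs.

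**1. Is there a baseline?** In Table 2 every laboratory safety row, bone mineral density and hepatitis B are ticked at screening, as are concomitant medication and the questionnaire. The adverse event row is not. The described content of the screening questionnaire has no physical symptoms. Elsewhere at screening there are a medical history, a physical examination and an exclusion for signs or symptoms of acute viral infection. None is described as recording the complaints asked about at follow-up.

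**2. Do text and table agree?** No. Study visits documents adverse events at each clinic visit and includes screening in the six visits. Read literally, that is six recordings; Table 2 schedules five.

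**3. Is there a comparator?** Nonusers are not marked for the adverse event row, and Safety assurance is written for PrEP users.

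**4. Does causality review cover self-reports?** Safety assurance ties the two-physician evaluation to adverse events on the case report form. Side effects are also collected by questionnaire. No section says that questionnaire reports are reviewed, and none says that they are not.

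**5. Illustration of how much step 4 matters.** Assumed inputs, none from the protocol:

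- b: chance that a participant reports a background complaint at one follow-up visit;
- s: share of such complaints removed by causality review;
- independence between visits.

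From the protocol: five follow-up visits (Table 2) and 1023 participants (Overview of study design; the Sample size section says 1000).

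Proportion with at least one counted complaint and no drug effect = 1 − (1 − b(1 − s))^5.

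| b | s = 0 | s = 0.5 | s = 0.9 | s = 1 |
|---|---|---|---|---|
| 2% | 1 − 0.98^5 = 9.6% | 1 − 0.99^5 = 4.9% | 1 − 0.998^5 = 1.0% | 0 |
| 5% | 1 − 0.95^5 = 22.6% | 1 − 0.975^5 = 11.9% | 1 − 0.995^5 = 2.5% | 0 |
| 10% | 1 − 0.90^5 = 41.0% | 1 − 0.95^5 = 22.6% | 1 − 0.99^5 = 4.9% | 0 |

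With s = 0 these are about 98, 231 and 419 of 1023 participants. At b = 5% the answer runs from 22.6% to zero depending on s alone, and s is what the protocol leaves open.

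**The case against.** The strongest reply is that attribution is already built in. The end point is limited to PrEP-related events, two physicians judge causality independently, and the sources are to be triangulated. An empty adverse event cell before the first dose is also normal, since a drug cannot cause an effect before it is taken. The protocol's descriptions of the questionnaires are one-sentence summaries, and item lists and counting rules are often left to the instrument, the case report form or the analysis plan.

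Much of this stands. A reader might infer that background symptoms are in fact counted as PrEP side effects, or that self-reports bypass physician review. The documents support neither: they are silent on whether the review covers questionnaire data. A reader might also infer that nothing about symptoms is recorded at screening. That is too absolute, given the history, the examination, the check for acute infection and the wording in Study visits. Nor can a multiplier for overstatement be put on the result: any such multiplier needs assumed background and true rates, and a large one also assumes no attribution at all.

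The reply does not remove two points. Physicians who judge relatedness have no systematic record of whether a complaint preceded the drug. And although an analysis plan can settle how events are counted, it cannot supply a baseline that the visit schedule does not collect. The blank interview cell is not itself the error; the gap is that the questionnaire already completed at screening is not described as carrying the symptom items used later.

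**Conclusion.** The point holds in limited form. No structured symptom baseline before PrEP is scheduled, nonusers are not marked to supply a comparison, Study visits and Table 2 disagree on whether adverse events are recorded at screening, and it is not stated whether questionnaire side effects are judged for causality before they enter the combined rate. Background symptoms may therefore inflate that rate.

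The size cannot be derived from the documents. In the illustration it runs from nil, when attribution is complete, to 41.0% of users when b is 10% and nothing is removed. Those figures rest on assumed inputs and independent visits and show only sensitivity; they are not predictions.

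Laboratory and bone mineral density outcomes have screening values and are not affected. This is a low-cost improvement to data collection plus a clarification. It does not show that the safety result will be wrong.

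**What to change.** 1. Add the symptom items used at follow-up to the questionnaire completed at screening. Ticking the interview cell in Table 2 would not by itself do this, because the questionnaire is a separate row.
2. Reconcile Study visits with Table 2 on whether adverse events are recorded at screening.
3. In Table 4, replace the joint rate by two: self-reported symptoms that are new or worse than at screening, and adverse events judged PrEP-related by the physicians.

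The cost is about a minute of participant time at a visit that already takes place, and short edits to Tables 2 and 4. No visit or test is added. Men already enrolled would lack the baseline, so the new-or-worse count would apply only to those enrolled after the change.
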